### Randomization

Enrolled dyads will undergo 1:1 block randomization by each study clinic performed by the Anglia Ruskin Clinical Trials Unit (ARCTU) to assign them to the intervention group or the control group. Randomization will be undertaken using an internet-based randomization system setup by ARCTU on the TENALEA system provided by FormsVision BV. The system stores the predetermined sequence of randomization; this list is not available to the investigators.

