### Control Group

The control group will only receive their TAU. There are different conditions and diseases and the treatment can vary widely among the participants. In addition, there are different health care systems among study centers. In any case, the participants in the control group will receive the TAU that they would receive at their care center regardless of the study.

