#### Primary Outcome Analysis

The primary analysis will be the comparison of total QoL-AD score mean changes (at 18 months) between intervention group and control group using a 2-sample, 2-sided Monte Carlo permutation *t* test. The use of a permutation test will avoid the need for strong assumptions about the distribution of the data. Similarly, a bootstrap approach will be used to obtain the 95% confidence limits for the difference between the group means.

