#### Secondary Outcome Analyses

The comparison between intervention group and control group for continuous variables will be analyzed with the same method described above, and categorical variables will be analyzed using Fisher exact test.

Regression analysis will be used to assess the relationship between the primary and secondary outcome measures and the Technology Familiarity Score to analyze whether prior experience of technology has an effect on the outcomes. Furthermore, a regression analysis will be used to assess the relationship between the primary and secondary outcome variables and the usage variables to indicate which aspects of the computer tablet use most affected the outcomes.

A user-behavior analysis will be performed to assess how users interact with the platform and how their behavior affects its efficacy. Specifically, we will assess and analyze the frequency of access to the SMART4MD app, the length of this interaction, and the quality of the inputs provided. These data will be correlated with users’ reminder schedules to explore differences between proactive and reactive use of the platform and will be followed over time to understand how increasing familiarity with the platform affects user behavior. In addition, the data will be used to improve the SMART4MD app, if necessary, to optimize user interaction. The results of the usability tests will be analyzed using statistical methods to quantify the error rate, effectiveness, and learning curve of the SMART4MD app and functions. For this, the intervention group will be asked to perform specific tasks with the app, and different interaction parameters will be measured such as number of taps, reaction time, time to target, time to accomplish, etc.

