#### Subgroup Outcome Analyses

Checks for the consistency of the intervention effects across sites will be done using a 2-way analysis of variance with the 2 factors being group (intervention/control) and site. Similarly, a subgroup analysis will be carried out according to the severity of cognitive impairment. These subgroups will be formed based on the MMSE score corrected by educational level and age.

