#### Adjusted Analyses

A secondary analysis will be an analysis of covariance to compare the 18-month total QoL-AD score means, where the response variable will be the 18-month total QoL-AD score and the covariate will be the baseline total QoL-AD score. This analysis will provide a comparison of the 18-month total QoL-AD score means adjusted for the baseline total QoL-AD score. Again, the *P* value will be obtained using a Monte Carlo permutation method, and the 95% confidence limits for the adjusted difference between the means will be obtained using a bootstrap approach.

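### Dyads are block-randomised within clinic but the group comparisons ignore clinic; where clinics differ in mean 18-month QoL-AD change, the primary test is conservative and precision is lost

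*Protocol article*

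**What the plan says.** - **Allocation.** Randomization: "Enrolled dyads will undergo 1:1 block randomization by each study clinic". A central web system holds the sequence. I read this as stratification by clinic.
- **Primary test and interval.** Primary Outcome Analysis compares mean change at 18 months by a "2-sample, 2-sided Monte Carlo permutation" t test, and "a bootstrap approach will be used to obtain the 95% confidence limits for the difference between the group means".
- **Secondary outcomes.** Under Secondary Outcome Analyses, comparisons "for continuous variables will be analyzed with the same method described above", and "categorical variables will be analyzed using Fisher exact test".
- **Adjusted analysis.** Adjusted Analyses describes an ANCOVA of the 18-month score in which "the covariate will be the baseline total QoL-AD score". No other term is named.
- **Use of site.** Only under Subgroup Outcome Analyses: "Checks for the consistency of the intervention effects across sites will be done using a 2-way analysis of variance", with group and site as the factors.
- **Differences between centers.** Control Group: "In addition, there are different health care systems among study centers". Setting lists four centers in three countries, and the Discussion expects available support to differ considerably between them.

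**The concern.** Clinic is a randomisation stratum, but no group comparison respects it. An unrestricted two-sample shuffle moves labels across clinics and countries, so its reference distribution contains allocations that the design ruled out.

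Blocking within clinic keeps clinic differences out of the treatment contrast. An unrestricted permutation or pooled bootstrap nevertheless leaves those differences in the error variance. The standard error is then overstated, the true size of the test falls below its nominal level, and the interval is wider than it need be.

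The article expects care to differ between centers, so some clinic differences in outcome are plausible. What is at stake is precision and a little power, not false positives.

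**Working it through.** **Inputs from the article (Sample Size):** standardised effect 0.2, two-sided 5% level, 80% power, 394 per group before dropout, 20% dropout, recruitment target 1200.

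**Assumed:** v, the share of variance in 18-month change that lies between clinics. The article gives no figure. Values of 0%, 2%, 5% and 10% are shown.

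**1. The plan's own figure.** By the normal approximation, n = 2(1.960 + 0.842)²/0.2² = 392.5, rounded up to 393. The t-based solution is 393.4, rounded up to 394. With dropout, 394/0.8 = 492.5, rounded up to 493. Both stated figures reproduce.

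**2. Effect of ignoring clinic.** With arms balanced within clinic, true SE = nominal SE × √(1 − v), where the nominal SE is the one that the unstratified test uses. Hence:
- Interval width relative to the correct width: 1/√(1 − v).
- Actual size: 2[1 − Φ(1.96/√(1 − v))].
- Power, unstratified: Φ[(0.2/SE − 1.96)/√(1 − v)].
- Power, stratified: Φ[0.2/(SE√(1 − v)) − 1.96].

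At 394 per group, SE = √(2/394) = 0.0712 in SD units, so 0.2/SE = 2.807.

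| v (assumed) | Interval too wide by | Actual size | Power, unstratified | Power, stratified | Gain (points) |
|---|---|---|---|---|---|
| 0% | 0% | 5.0% | 80.2% | 80.2% | 0 |
| 2% | 1.0% | 4.8% | 80.4% | 80.9% | 0.5 |
| 5% | 2.6% | 4.4% | 80.8% | 82.1% | 1.3 |
| 10% | 5.4% | 3.9% | 81.4% | 84.1% | 2.7 |

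Worked line for v = 5%: √0.95 = 0.9747. Width ratio 1/0.9747 = 1.026. Size 2[1 − Φ(2.011)] = 0.0443. Power Φ(0.847/0.9747) = 0.808 against Φ(2.807/0.9747 − 1.96) = 0.821.

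**3. Simulation.** I assumed four equal clinics and 396 per arm, used the permutation variances with and without restriction to clinic, and ran 40,000 null trials per value of v. Unstratified size was 5.1%, 4.8%, 4.5% and 3.9% at v = 0%, 2%, 5% and 10%. Restricted to clinic, it was 5.0% to 5.1% throughout. A much smaller run of explicit permutations (1,500 trials per value) was noisier. At v = 10% it gave 4.7% unstratified and 6.4% within clinic, with a Monte Carlo error of about √(0.05 × 0.95/1500) = 0.6 points.

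**4. At the recruitment target.** 1200 × 0.8/2 = 480 per group. Power, unstratified against stratified, is 87.5% and 87.9% (v = 2%), 87.9% and 88.9% (5%), and 88.5% and 90.4% (10%).

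**5. Fisher test.** With 396 per arm and an assumed common rate of 44% in every clinic, simulated size is 4.1%, so there is conservatism with no clinic difference at all. With assumed clinic rates of 24%, 37%, 51% and 64%, it is 2.9%.

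**The case against.** **The effect may be negligible.** The primary outcome is a change score, which removes stable differences in level between clinics. The article describes differing health systems and usual care, not differing change in QoL-AD. This stands: v could be near zero, and at v = 0 nothing is lost. A reader might infer that the planned P values and limits are conservative whatever the data. The article does not support that, because the direction also needs arms that stay roughly balanced within clinic after dropout.

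**No planned property fails.** This also stands. A reader might infer that the trial is underpowered or its test invalid. Neither follows: under these conditions size stays at or below 5%, and because the sample size was computed from the total SD, the unstratified test still reaches 80%.

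**Re-enacting the randomisation is not the article's stated reason for permuting.** It permutes to avoid distributional assumptions. Moreover, shuffling freely within clinic still only approximates a blocked allocation. Both are true, but within-clinic shuffling is much closer to the design than shuffling across countries.

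**The Fisher test is conservative anyway.** Partly right. Its conservatism should not be put down to clinic alone, since discreteness accounts for the 4.1% seen with equal rates.

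**Site is handled, and the rest is detail for the analysis plan.** The two-way ANOVA could yield a site-adjusted group effect, but it is labelled a consistency check and does not replace the primary test. The analysis plan is not at hand and may restrict the resampling. The article, however, names the test, the interval method and the single covariate, and it mentions site where site is meant. Its plain reading is unstratified.

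**Conclusion.** The mismatch between design and analysis is in the text: clinic governs the allocation and is absent from every between-group comparison apart from the consistency check. The loss runs from nothing at v = 0% to an interval 5.4% too wide and 2.7 points of power at v = 10% with 394 per group. At 480 per group the gain from stratifying at v = 10% is about 2 points. These sizes rest on an assumed between-clinic share, on balance within clinic after dropout, and on reading the allocation as stratified by clinic. This is a worthwhile efficiency improvement in a safe direction, not a threat to the validity of the trial.

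**What to change.** - **Primary and continuous secondary outcomes:** permute group labels within clinic, or within block if block identifiers are available. Bootstrap within clinic and group.
- **ANCOVA:** add clinic as a factor alongside baseline QoL-AD, with the same restricted resampling.
- **Categorical outcomes, including adherence:** replace the Fisher test with a clinic-stratified Cochran-Mantel-Haenszel test, in its exact form if the tables are sparse.
- **Small clinics:** pool very small clinics within country by a rule set before unblinding.

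The cost is a few sentences in the analysis section and a few lines of code. Clinic must already be recorded for the randomisation, and no extra data or participants are needed. If clinics turn out not to differ, essentially nothing is lost by having stratified.

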#### Secondary Outcome Analyses

The comparison between intervention group and control group for continuous variables will be analyzed with the same method described above, and categorical variables will be analyzed using Fisher exact test.

Regression analysis will be used to assess the relationship between the primary and secondary outcome measures and the Technology Familiarity Score to analyze whether prior experience of technology has an effect on the outcomes. Furthermore, a regression analysis will be used to assess the relationship between the primary and secondary outcome variables and the usage variables to indicate which aspects of the computer tablet use most affected the outcomes.

A user-behavior analysis will be performed to assess how users interact with the platform and how their behavior affects its efficacy. Specifically, we will assess and analyze the frequency of access to the SMART4MD app, the length of this interaction, and the quality of the inputs provided. These data will be correlated with users’ reminder schedules to explore differences between proactive and reactive use of the platform and will be followed over time to understand how increasing familiarity with the platform affects user behavior. In addition, the data will be used to improve the SMART4MD app, if necessary, to optimize user interaction. The results of the usability tests will be analyzed using statistical methods to quantify the error rate, effectiveness, and learning curve of the SMART4MD app and functions. For this, the intervention group will be asked to perform specific tasks with the app, and different interaction parameters will be measured such as number of taps, reaction time, time to target, time to accomplish, etc.

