### Intervention: the Support Monitoring and Reminder Technology for Mild Dementia Platform

Our intervention strategy, which aims to improve the QoL of PwMCI, is based on the use of a single or multiple function that the SMART4MD app enables. The rationale behind and description of the functionalities of the SMART4MD app are presented in detail in a separate document (Multimedia Appendix 1). Briefly, participants in the intervention group will be provided with a data-enabled computer tablet preinstalled with the SMART4MD app. The tablet will be configured in such a way that it is not possible for participants to download any other app or software onto the tablet.

SMART4MD is a general electronic health app that has been adapted specifically for MCI through a structured process involving the participation of PwMCI and their informal carers and health care professionals. Focus groups were conducted with PwMCI and their informal carers, and interviews were conducted with health care professionals. The app can run both on tablet and mobile phone devices adopting the Android operating system but is specifically optimized for tablet devices as opposed to smaller screen mobile phone devices.

The core functionalities of the app are based on reminders (medication, appointments with health care providers, and meeting up with family and friends), cognitive supporting activities (clock, calendar, brain games, and photos) and optional status and health information sharing with family and informal carers (including mood and specific health problems such as headaches).

The app allows the participant to share health information to other people of their choice (relatives or research team) by email. The participant can select what kind of information he/she can share and to whom he/she wants to send this information.

An important feature of SMART4MD is its personalization facility: main users (PwMCI and informal carers) will be able to switch on/off or change various features and information-sharing possibilities.

The app is intended to be used daily at home, mainly by the PwMCI themselves, with the help of their informal carers when needed.

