##### User Behavior

In the intervention group, the following data will be collected from the platform: date and time of any interaction with the SMART4MD app, length of interaction, and the functions used during the interaction.

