### Follow-Up Visits

There will be 3 follow-up visits at 6, 12, and 18 months after baseline interview. A summary of visits’ assessments is shown in Table 1. In addition, to measure medication adherence, there will be a preadherence phone call in each follow-up visit (30 days before the visit).

**Table 1 table1:** Schedule of events.

Events, assessments, and data collection	Screening	Baseline	Tablet delivery	Month 6 ±18 days	Month 12 ±18 days	Month 18 ±18 days
Informed consent (PwMCI^a^ and informal carer)	X^b^	—^c^	—	—	—	—
Review of inclusion and exclusion criteria (PwMCI)	X	—	—	—	—	—
Demography (PwMCI and informal carer) and medical history (PwMCI)	—	X	—	—	—	—
Introduction and training for Support Monitoring and Reminder for Mild Dementia (intervention group only, PwMCI and informal carer)	—	—	X	—	—	—
Geriatric Depression Scale (PwMCI)	X	—	—	X	X	X
Mini-Mental State Examination (PwMCI)	X	—	—	X	X	X
Quality of Life in Alzheimer's Disease scale (PwMCI)	—	X	—	X	X	X
Instrumental Activities of Daily Living (PwMCI)	—	X	—	X	X	X
Adherence to prescribed medication (PwMCI)	—	X	—	X	X	X
EuroQol-5D (PwMCI and informal carer)	—	X	—	X	X	X
Attendance at appointments and admissions (PwMCI)	—	X	—	X	X	X
Familiarity with tech survey (PwMCI and informal carer)	—	—	X	—	—	—
QoL-AD on behalf of PwMCI (informal carer)	—	X	—	X	X	X
Zarit Caregiver Burden Interview (informal carer)	—	X	—	X	X	X
User satisfaction survey (intervention group only, PwMCI, and informal carer)	—	—	—	X	X	X
User behavior (intervention group only, informal carer, and PwMCI)	—	—	—	X	X	X

^a^PwMCI: persons with mild cognitive impairment.

^b^The instrument is used at this time point.

^c^The instrument is not used at this time point.

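### The regression of outcomes on app use is given a causal purpose that self-selected, post-randomisation use within one arm cannot support

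*Protocol article*

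**What the plan says.** Under Secondary Outcome Analyses, the protocol article states that "a regression analysis will be used to assess the relationship between the primary and secondary outcome variables and the usage variables", and gives the purpose as "to indicate which aspects of the computer tablet use most affected the outcomes". The next paragraph adds a user-behaviour analysis of "how users interact with the platform and how their behavior affects its efficacy".

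Three other sections describe the exposure:

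- **Who has it.** User Behavior: "In the intervention group, the following data will be collected from the platform", namely the timing and length of each interaction and the functions used. Under Control Group, controls receive only their usual treatment.
- **Who chooses it.** The intervention section says that "main users (PwMCI and informal carers) will be able to switch on/off or change various features and information-sharing possibilities". It also says that carers help when needed.
- **When it is collected.** Table 1 (Follow-Up Visits) schedules user behaviour at months 6, 12 and 18, the visits at which QoL-AD and the other outcomes are measured.

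The article does not call the usage regression exploratory or associational. It gives no covariates for it, no usage window, and no statement of whether score or change is the response.

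**The concern.** The stated purpose is to say which aspects of use affected the outcomes. A regression on use answers that only if people who use the app more are otherwise comparable with those who use it less. Here there are two reasons to doubt it.

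- **Confounding.** Better cognition or mood, familiarity with technology, and an engaged carer can each plausibly raise use and also go with a better outcome. The article itself plans to test whether technology familiarity has an effect on the outcomes.
- **Reverse causation.** A person who declines may stop using the app. If use and outcome cover the same period, decline then appears as a result of low use.

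At stake is what the trial can say about which functions work. The article also says that the usage data will be used to improve the app where necessary, so a misread association could have practical consequences.

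**Working it through.** **No figure to reproduce.** The article gives no number for the usage analysis. The question is whether the stated conclusion can follow from the stated data, and the arithmetic below only illustrates how small a dependence would be enough to mislead. All correlations are assumptions; the article gives none.

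**Inputs from the article.** Target 1200 dyads, 1:1 allocation, 20% dropout, 394 evaluable per group, QoL-AD SD about 7, effect size 0.2. Users with an outcome if the target is met: 1200 / 2 × 0.8 = 480.

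**Model A: baseline status drives use; use has no effect.** All variables are standardised. Let a be the correlation of use with the baseline score, and 0.5 the correlation of the baseline with the 18-month score. The induced correlation of use with the 18-month score is ρ = 0.5a. The chance of a two-sided 5% result is approximately P(|Z + m| > 1.96), with m = atanh(ρ) × √(n − 3) and n = 480.

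| a | ρ | m | Falsely significant |
|---|---|---|---|
| 0.1 | 0.05 | 1.09 | 19% |
| 0.2 | 0.10 | 2.19 | 59% |
| 0.3 | 0.15 | 3.30 | 91% |

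Simulation (4,000 trials per setting) gives the same 19%, 59% and 91%. Adjusting for baseline brings the rate back to about 5%, because in this model baseline is the only confounder.

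**Model A with change as the response.** Primary Outcome Analysis compares mean changes. The covariance of use with change is 0.5a − a = −0.5a, and the variance of change is 1 + 1 − 2 × 0.5 = 1. The induced correlation is therefore −0.5a: the same size, with the opposite sign. False-positive rates are essentially the same (about 18%, 59% and 92% by simulation), but greater use now looks harmful.

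**Model B: an unmeasured factor correlates r with both use and QoL change.** The induced correlation is r². With n = 394, simulation gives:

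| r | Induced correlation | Spurious slope, points per SD of use | Falsely significant |
|---|---|---|---|
| 0.1 | 0.01 | 7 × 0.01 = 0.07 | 6% |
| 0.2 | 0.04 | 7 × 0.04 = 0.28 | 13% |
| 0.3 | 0.09 | 7 × 0.09 = 0.63 | 44% |

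**Model C: decline itself reduces use, with correlation r.** With n = 394 the rates are about 52%, 98% and 100% for r = 0.1, 0.2 and 0.3. The spurious slopes are 7r = 0.7, 1.4 and 2.1 points per SD of use. For scale, the between-group difference the trial is sized for is 0.2 × 7 = 1.4 points.

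**Does another planned analysis cover this?** No. The intention-to-treat principle and the analysis of covariance on baseline QoL-AD (Adjusted Analyses) concern the comparison of randomised groups. The article does not say in so many words that the usage regression is confined to the intervention arm; that follows from where use is recorded. If controls were entered with zero use, allocation and self-selection would be mixed together, and the difficulty would remain.

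**The case against.** The strongest reply is that the article specifies no model. Covariates and usage windows commonly sit in a full protocol or analysis plan, and there are signs pointing towards adjustment. Sociodemographics, medical history, GDS-15, technology familiarity and user behaviour all appear under a covariables heading; the missing-data section mentions multiple regression; interactions are time-stamped; and use is to be followed over time. This stands. A reader might infer that the plan is an unadjusted regression on cumulative 18-month use, but the text does not say so, and the absence of a covariate list is not the fault here.

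It is also fair that some of the wording is associational, that efficacy rests on the randomised comparison, and that the rates above depend on assumed correlations. Two further stronger readings should be set aside. One is that the analysis would credit whichever functions healthier users prefer: in Model A this holds for the 18-month score but reverses for change, and the article does not say which is regressed. The other is that a dose-response among users would be put forward in place of a null trial result: nothing in the article plans this.

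What the objection does not remove is the stated purpose. The phrases "to indicate which aspects of the computer tablet use most affected the outcomes" and "how their behavior affects its efficacy" claim effects. Covariates alone would not secure that claim, because decline during follow-up can itself change later use.

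**Conclusion.** The point holds as a mismatch between stated purpose and design. Use is self-selected, recorded in one arm only, and collected after randomisation alongside the outcomes, so a regression on it can show association but cannot establish which aspects of use affected the outcomes. An apparent effect could arise in either direction when use does nothing.

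The size of the bias is unknown because the model is not stated. Under the assumed confounding models the false-positive rate runs from about 6% to 44% (Model B, 394 users) or about 19% to 91% (Model A, 480 users, unadjusted). These figures show that modest correlations are enough; they are not properties of this plan. The randomised primary comparison, its sample size and its intention-to-treat basis are unaffected. This should be corrected, but it does not threaten the main result.

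**What to change.** 1. **Wording.** Label the usage analysis exploratory. Replace both causal phrases with *were associated with*, and state that no efficacy conclusion will be drawn from use within the intervention arm.
2. **Time order.** Relate use up to month 6 to outcomes at months 12 and 18.
3. **Adjustment.** Include the baseline and month-6 values of the outcome, MMSE and GDS-15 at entry (Table 1 takes both at screening), age, education, Technology Familiarity Score (Table 1 takes it at tablet delivery) and site. State whether score or change is the response.

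All of these data are already scheduled, so the cost is text and a few model terms, with no new visit or participant. There are downsides. Use after month 6 is left out of the main usage model, and adjusting for the month-6 value removes any association already present by then. Residual confounding also remains, for example by carer involvement, so the associational wording is needed even with the adjusted, time-ordered model.
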